#### Statistical Analysis

The primary feasibility outcomes will be reported descriptively with percentage, mean or median, standard deviation, or 95% confidence interval. As a pilot, the study is not powered to detect a statistically significant difference between groups. The treatment effect will be assessed with mean difference between two groups and confidence intervals of 75%, 85%, and 95%. A figure showing these CIs, minimum important difference, and the null value will help assess both statistical significance and the potential for clinical significance (Bell et al., 2018). All analyses will be conducted according to the intention-to-treat principle. Last observation carried forward will be used for imputing missing data because tinnitus is a chronic and constant symptom. Descriptive statistics will be computed for each of the analyzed variables. Exploratory inferential analysis will be performed using repeated-measures ANCOVA. Mean differences from baseline to end of treatment in each group will be examined by paired *t*-test or Wilcoxon signed rank test. Subgroup analysis on those with or without hearing loss, and those with unilateral or bilateral tinnitus will be made. All statistical tests will be two-sided, and *p* < 0.05 is considered statistically significant. The statistical software of SPSS 23.0 will be used for analysis.

Adverse events will be categorized and percentage of those experiencing some adverse events and serious adverse events will be documented. Chi-square tests will be performed to examine differences in the proportion of total and categories of adverse events within each group.

It is anticipated to find some preliminary evidence about the clinical effectiveness of BHT on chronic tinnitus, to identify if it is feasible to conduct a full-scale RCT of BHT and necessary changes to the protocol if possible. Statistical comparisons between groups may be misleading due to the many potential problems arising from small samples and low power. The results from statistical comparisons will be treated with great caution, and reported only with explicit reference to statistical power.

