#### Secondary Outcome Measures

A comprehensive set of outcome measures is employed to assess mainly the following six domains: tinnitus percept, impact of tinnitus, co-occurring complaints, quality of life, and treatment-related outcomes (Hall et al., 2016).1) Tinnitus Handicap Inventory in Chinese (Cantonese) version (THI-CH)

THI-CH is a 25-item self-administered questionnaire to quantify the impact of tinnitus on daily life. It has been demonstrated to be a reliable and valid measure of self-perceived tinnitus-related distress (Kam et al., 2009).2) Tinnitus functional index in Chinese (Cantonese) version (TFI-CH)

TFI-CH is a 25-item self-administered questionnaire that assesses eight domains of tinnitus impact: intrusiveness, sense of control, cognition, sleep, auditory, relaxation, quality of life, and emotion. It has been demonstrated to be a reliable and valid measure for intake assessment and treatment-related changes (Kam et al., 2018).3) Tinnitus sensation level

The tinnitus pitch and loudness matching will be measured according to Vernon and Meikle’s procedure (Vernon and Meikle, 2003).4) Self-rated visual analogue scale (VAS) on tinnitus loudness and annoyance (McCormack et al., 1988)

VAS is a validated and reliable tool for measuring subjective experience in tinnitus loudness and annoyance (Vernon and Meikle, 2003). It will be measured per ear. If a subject has bilateral tinnitus, the VAS will be measured differently for each side.5) Chinese (Cantonese) version of the Pittsburgh Sleep Quality Index (CPSQI)

The CPSQI is a self-rating questionnaire used to measure the quality and patterns of sleep in adults (Tsai et al., 2005).6) Chinese (Cantonese) version of Hospital Anxiety and Depression Scale (HADS)

The Chinese HADS is a 14-item questionnaire designed to assess the severity of mild, even sub-syndromal degrees of anxiety and depression (Leung et al., 1999).7) Adverse events

Adverse events will be recorded and coded to preferred terms as defined by the Medical Dictionary for Regulatory Activities (MedDRA), version 22.0.

All measurements will be taken at baseline, end of treatment (8 weeks after the first day of treatment), and after the 4-week follow-up. Kidney function will be examined before and after the treatment on those receiving BHT.

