#### Sample Size Estimation

As an exploratory pilot study, the stepped rules of thumb is used for estimating the pilot sample size (Whitehead et al., 2016; Bell et al., 2018). Although there is no previous study on BHT, we base the estimation of standardized effect size on two previous studies of compound TCM formula on chronic tinnitus (Lin et al., 2015; Chen et al., 2018). Using a mean difference estimate of eight and an estimate of standard deviation of 11–20 in similar populations, the standardized effect size is about 0.4 to 0.7. Assuming a reasonably medium (0.3–0.7) standardized effect size, a sample size of 10 per arm for the pilot is recommended for a 90% powered main trial. Therefore, a total of 24 patients will be needed in this trial, considering a 20% dropout rate.

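### The main efficacy confidence intervals are not tied to the planned baseline-adjusted model; linking them would usually give narrower intervals and protect against chance imbalance

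*Protocol article*

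**What the plan says.** All references are to the protocol article.

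- **Effect estimate (Statistical Analysis).** "The treatment effect will be assessed with mean difference between two groups and confidence intervals of 75%, 85%, and 95" per cent. The next sentence puts these intervals in a figure with the minimum important difference and the null value, to help judge statistical and potential clinical significance.
- **Second between-group analysis (same section).** "Exploratory inferential analysis will be performed using repeated-measures ANCOVA". Its covariates are not named, and nothing says that the plotted intervals come from it.
- **Within-group analysis (same section).** "Mean differences from baseline to end of treatment in each group will be examined by paired" t-test or Wilcoxon signed rank test.
- **Baseline data (Secondary Outcome Measures).** "All measurements will be taken at baseline, end of treatment (8 weeks after the first day of treatment), and after the 4-week follow-up". This gives a baseline score for every efficacy scale. Adverse events are on the same list but have no baseline score, and neither do the three primary feasibility outcomes.
- **Size (Sample Size Estimation).** "Using a mean difference estimate of eight and an estimate of standard deviation of 11–20 in similar populations"; "a sample size of 10 per arm for the pilot is recommended for a 90% powered main trial"; "a total of 24 patients will be needed in this trial, considering a 20% dropout rate".
- **Analysis set and allocation.** Intention-to-treat with last observation carried forward (Statistical Analysis). Block randomisation, with no stratification mentioned (Randomization and Blinding).

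**The concern.** The interval figure is the plan's tool for judging whether the formula may have a clinically relevant effect. The Discussion says the effect estimates will inform the planning of a full-scale trial. As worded, the figure rests on a plain difference between group means, and the one model that could use the baseline scores sits apart from it.

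Two things follow if the difference is an unadjusted contrast of final scores. First, at this sample size the arms can easily differ at baseline by chance, and part of that difference carries into the estimate. Second, the intervals give up whatever precision the baseline scores could supply. A third consequence holds on any reading: the plan allows two between-group estimates for the same scale and does not say which one is plotted.

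**Working it through.** **Inputs.** Mean difference 8, SD 11 to 20, 10 per arm, 20% dropout, total 24 (Sample Size Estimation). Tests are two-sided (Statistical Analysis). Assumptions, because the documents are silent: 1:1 allocation; 11 to 20 serves as both the baseline and the final-score SD; the baseline-to-outcome correlation ρ ranges from 0 to 0.8.

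**The plan's own figure.** 8/20 = 0.40 and 8/11 = 0.73, matching the stated effect size of about 0.4 to 0.7. 10 × 1.2 = 12 per arm, so 24 in total, as stated. Under intention-to-treat with last observation carried forward, all randomised patients are analysed, so n = 12 per arm is used below.

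**Chance baseline imbalance.** SD of the difference in baseline means = √(2/12) = 0.408 SD units. In points this is 0.408 × 11 = 4.5 to 0.408 × 20 = 8.2, against an assumed effect of 8. The probability of exceeding 0.5 SD in either direction is 2 × [1 − Φ(0.5/0.408)] = about 0.22. A final-score difference carries a share ρ of the imbalance into the estimate. At ρ = 0.5, an imbalance of one such SD shifts it by 0.5 × 4.5 = about 2.2 points to 0.5 × 8.2 = 4.1 points.

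**95% half-widths at a single time point.**

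- Unadjusted final score: t(0.975, 22) × SD × √(2/12) = 0.847 × SD, which is 9.3 points at SD 11 and 16.9 at SD 20.
- Baseline-adjusted: t(0.975, 21) × SD × √(2/12) × √(1 − ρ²) × √(1 + 1/20). The last factor allows for chance baseline imbalance.
- Change score relative to final score: √(2(1 − ρ)).

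| Assumed ρ | Adjusted ÷ final score | Change ÷ final score | Adjusted half-width, SD 11 to 20 |
|---|---|---|---|
| 0 | 1.03 | 1.41 | 9.6 to 17.4 |
| 0.2 | 1.01 | 1.27 | 9.4 to 17.1 |
| 0.3 | 0.98 | 1.18 | 9.1 to 16.6 |
| 0.5 | 0.89 | 1.00 | 8.3 to 15.1 |
| 0.6 | 0.82 | 0.89 | 7.7 to 13.9 |
| 0.7 | 0.73 | 0.77 | 6.8 to 12.4 |
| 0.8 | 0.62 | 0.63 | 5.7 to 10.4 |

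The ratios for the 75% and 85% intervals are almost the same.

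**Break-even.** Adjusted and unadjusted widths are equal at ρ of about 0.23 with 12 per arm, and about 0.26 with 10 per arm.

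**Against change scores.** From unrounded ratios, adjusted ÷ change is 0.890/1.000 = 0.89 at ρ = 0.5, 0.822/0.894 = 0.92 at 0.6 and 0.734/0.775 = 0.95 at 0.7. The gain is therefore roughly 5% to 10%.

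**Simulation check.** In 10,000 simulated trials at 12 per arm the mean width ratios agreed with the formula (0.89 at ρ = 0.5, 0.73 at 0.7). The adjusted interval was the narrower one in 20% of trials at ρ = 0, 36% at 0.2, 52% at 0.3, 86% at 0.5 and 99% at 0.7.

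**The case against.** **The text does not say unadjusted.** A reader might infer that the plan specifies an unadjusted analysis. It does not: an adjusted difference from an ANCOVA is also a mean difference between groups, and the article does not say whether final scores or changes are compared. This stands as a limit on the wording of the point. The plain phrase, with the ANCOVA listed apart and labelled exploratory, still makes the unadjusted reading the natural one. If an adjusted difference was meant, the same sentence settles it.

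**The model is already planned, and an article may leave covariates to the analysis plan.** This is fair as to the covariate list. But the article does state which quantity feeds the figure, and that stated choice can be improved with a model it already names.

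**The gain is not guaranteed.** A reader might infer that the intervals are certainly wider than necessary. That depends on a correlation the documents do not give. The entry requirement of a Tinnitus Handicap Inventory score above 38 restricts the baseline range and may lower the correlation for that scale. In the other direction, the protocol calls tinnitus chronic and constant, and carrying a baseline value forward for someone lost before week 8 makes outcome equal baseline. If 20% were lost that way, with ρ = 0.5 in the rest and similar means and variances, overall ρ would be about 0.2 × 1 + 0.8 × 0.5 = 0.6.

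**These are secondary outcomes of a pilot.** The feasibility thresholds do not use the intervals, and the article promises caution with between-group comparisons. This stands and limits the weight of the point.

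**Conclusion.** The point holds as an improvement in efficiency and in protection against chance imbalance. The main efficacy display is tied to a mean difference most naturally read as unadjusted and is not linked to the planned ANCOVA, although every efficacy scale has a baseline score. The benefit is worthwhile from a correlation of about 0.5, negligible near 0.3, and reversed by at most about 3% at very low correlations. These sizes rest on 12 per arm, equal baseline and final-score SDs, and an assumed correlation.

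Two stronger readings are not supported. The simple difference is not biased: over repeated randomisations it is unbiased, and the concern is only with the imbalance that happens to occur in this one trial. Nor does the point extend to every outcome, because adverse events and the feasibility rates have no baseline value. The sample size of 24 is unaffected.

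**What to change.** In Statistical Analysis, state that for each efficacy scale the week-8 and week-12 between-group differences, and the 75%, 85% and 95% intervals in the figure, come from the planned repeated-measures ANCOVA. That model should have arm, week as the repeated factor, and the scale's own baseline score as covariate. Report the unadjusted difference as a supporting result.

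The cost is one sentence, no new data and one degree of freedom, with a slightly wider interval if the correlation turns out to be very low.

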We aim to evaluate the clinical efficacy and safety of TCM formula on chronic subjective tinnitus, in the hope of pursuing an effective treatment option for tinnitus. We have developed a TCM formula (BHT) for tinnitus based on previous studies and our clinical experience. An adequately powered RCT that compares TCM formula with placebo is appropriate to address the issue of efficacy; however, there is insufficient evidence to support a large full-scale RCT at present. Undertaking such a RCT raises important concerns including patients’ acceptance of TCM formula and adherence to treatment, as well as impact of TCM on the different aspects of tinnitus; furthermore, there is no previous study to provide some required parameters to design a definitive RCT. Therefore, we propose a small-scale pilot RCT to address whether a RCT of TCM formula for tinnitus is feasible with regard to (1) patient recruitment; (2) patient acceptability, (3) adherence to protocol, and (4) potential effectiveness of TCM formula. This pilot study is well justified by three main strengths on the study design. Firstly, a TCM formula BHT is developed based on the treatment principle of dredging the meridian passage and tonifying the essence of kidney, and prescribed to the subset of patients with corresponding TCM syndrome. Secondly, we will use validated and comprehensive scales to assess the impact and perception of tinnitus. Thirdly, we develop this study with scientific rigor following the CONSORT guideline extension to pilot study (Eldridge et al., 2016).

The natural course of subjective tinnitus varied considerably across individuals. The participants enrolled into clinical trials may demonstrate a small but statistically significant improvement, despite receiving no intervention (Phillips et al., 2018). A pilot randomized trial with controlled arm is more appropriate than an observatory study to provide preliminary data for further research. The results of this pilot study will inform a future full-scale RCT to establish the efficacy of TCM formula for chronic subjective tinnitus.

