#### Specific Inclusion and Exclusion Criteria of Study Subjects

##### Inclusion Criteria

1) Diagnosis of unilateral or bilateral subjective continuous (24 h) tinnitus with normal hearing or bilateral/unilateral mild to moderate hearing loss, i.e., an average pure-tone audiometry threshold for 500, 1,000 and 2,000 Hz between 0 dB HL and 55 dB HL;2) Aged between 18 and 60 years old;3) Tinnitus duration of at least 6 months;4) Moderate level of distress caused by tinnitus with scores above 38 on the Chinese (Cantonese) version of the Tinnitus Handicap Inventory (THI-CH) (Newman et al., 1996; Kam et al., 2009);5) Having the diagnosis of TCM syndrome of kidney essence deficiency and stagnation of Qi and blood flowing in the meridian, which may have symptoms or signs of low back pain or general fatigue, frequent urination, and dark or pale tongue.

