Following the treatment principle, we further combine Er Long Zuo Ci Pill with several other herbs with an effect of activating blood circulation, dredging the meridians, and tranquilizing the mind to make the formula BHT. In BHT, *Rehmannia glutinosa* (Gaertn.) DC (Orobanchaceae] (Dihuang), Cornus officinalis Siebold & Zucc (Cornaceae) (Shanzhuyu), and Dipsacus asper Wall. ex DC (Caprifoliaceae) (Xuduan) have the effect of tonifying kidney essence. Paeonia × suffruticosa Andrews (Paeoniaceae) (Mudanpi), Salvia miltiorrhiza Bunge (Lamiaceae) (Danshen), Conioselinum anthriscoides “Chuanxiong” (Apiaceae) (Chuanxiong), and Prunus persica (L.) Batsch (Rosaceae) (Taoren) have the effect of activating blood circulation. Poria cocos (Schw.) Wolf (Fuling), Bupleurum falcatum L (Apiaceae) (Chaihu), Pinellia ternata (Thunb.) Makino (Araceae) (Fabanxia), Pueraria *montana* var. lobata (Willd.) Maesen & S.M.Almeida ex Sanjappa & Predeep (Fabaceae) (Gegen), and Acorus calamus var. angustatus Besser (Acoraceae) (Shichangpu) have the effect of dredging the meridians. Ziziphus jujuba Mill (Rhamnaceae) (Suanzaoren), Magnetitum (Cishi), and Margaritifera Concha (Zhenzhumu) have the effect of suppressing hyperactive liver yang and tranquilizing the mind.

BHT is developed for those with the most common TCM syndrome, kidney essence deficiency, and stagnation of Qi and blood flowing in the meridian around the ears, in patients with chronic tinnitus. From the view of TCM, BHT is of generally neutral nature (not hot or cold), which enlarges the scope of its clinical application. During the study, the clinical symptoms and signs, pulse, and tongue diagnosis will be collected. Further analysis of its effects on those patients with TCM diagnosis of cold, warm, or cold–heat complication will be made.

The study results will provide an estimation of the general add-on treatment effect of CHM on chronic tinnitus. The choice of informative counseling alone as control will help to control some non-specific treatment effects, such as natural history and regression to the mean; however, it should be noted that the placebo effect could not be ruled out from the comparison results. The possible placebo effect of CHM may have effects on the outcomes, especially subjective ones. A placebo-control and some objective outcomes, such as functional near-infrared neuroimaging (fNIR), may be employed in the design of future full-scale RCT.

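### Last observation carried forward rests on tinnitus being constant, which the article itself contradicts; it scores anyone lost before week 8 as unchanged, biasing the BHT estimate and narrowing its intervals

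*Protocol article*

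**What the plan says.** The Statistical Analysis section fixes both the method and its reason: "Last observation carried forward will be used for imputing missing data because tinnitus is a chronic and constant symptom". No other missing-data method and no sensitivity analysis is named. The carried-forward data feed the between-group mean difference with its 75%, 85% and 95% intervals, the repeated-measures ANCOVA and the within-group paired tests.

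On the course of the condition, the Introduction says: "The natural course of subjective tinnitus varied considerably across individuals". It adds that trial participants "may demonstrate a small but statistically significant improvement, despite receiving no intervention". The Discussion defends the counselling-only control because it "will help to control some non-specific treatment effects, such as natural history and regression to the mean".

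On timing, the Secondary Outcome Measures section says: "All measurements will be taken at baseline, end of treatment (8 weeks after the first day of treatment), and after the 4-week follow-up".

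**The concern.** Carrying a value forward assumes that the patient's score would have stayed where it was last seen. The article gives constancy of tinnitus as the ground for this, yet elsewhere expects severity to move through natural history, regression to the mean or treatment. With no outcome visit between baseline and week 8, the last observation for anyone lost during treatment is the baseline value, so the method becomes an assumption of exactly zero change.

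At stake are the clinical estimates the pilot is meant to hand on. The Introduction says no earlier study supplies the parameters needed for a definitive trial, and the Discussion says the effect estimates will inform its planning. The promised caution about between-group comparisons concerns small samples and low power; it does not cover bias from imputation.

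**Working it through.** **Inputs from the article.** Difference 8 and SD 11 to 20 (Sample Size Estimation); 24 patients, so 12 per arm, with 20% dropout (same section); outcome visits at baseline, week 8 and week 12.

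**Assumptions, not in the article.** Dropout occurs before week 8 and is unrelated to outcome; its split by arm; a control-arm improvement m of 0, 3 or 8 points; the quoted SD taken as the SD of change; a baseline SD where needed.

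**The article's own figures.** 8/20 = 0.40 and 8/11 = 0.73, which matches "the standardized effect size is about 0.4 to 0.7". 10 per arm gives 20, and 20 × 1.2 = 24, as stated.

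**Bias in the difference.** Let d_T and d_C be the proportions lost in the BHT and control arms. True mean improvements are m + 8 and m. Carry-forward gives

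(1 − d_T)(m + 8) − (1 − d_C)m = 8(1 − d_T) + m(d_C − d_T).

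| Lost, BHT / control | m = 0 | m = 3 | m = 8 |
|---|---|---|---|
| 20% / 20% | 6.4 | 6.4 | 6.4 |
| 30% / 10% | 5.6 | 5.0 | 4.0 |
| 10% / 30% | 7.2 | 7.8 | 8.8 |

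With equal loss the result is dilution whatever m is. In the last row the estimate exceeds the true 8 once m is above 4, because 7.2 + 0.2m > 8. With no true effect the formula reduces to m(d_C − d_T): at 10%/30% and m = 3, that is 0.6 points in favour of BHT where there is none.

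**Interval width.** Take 12 per arm with 2 missing in each, scored as zero change. The expected sample variance of change in an arm with mean change μ and SD s is (9.167s² + 1.667μ²)/11 = 0.833s² + 0.152μ². With m = 0 (arm means 0 and 8):

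- s = 11: 100.8 + 4.8 = 105.7, SD 10.28. The 95% half-width is 2.074 × 10.28 × √(2/12) = 8.70, against 2.101 × 11 × √(2/10) = 10.34 from the 10 observed per arm, so 16% narrower.
- s = 20: SD 18.39, half-width 15.57 against 18.79, so 17% narrower.

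With m = 3 the reductions are 14% and 17%. With m = 8 and s = 11 the reduction is 8%. The interval is too narrow and is also centred below 8: (10/12) × 8 = 6.67.

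**SD of change at 20% missing.** Per arm, variance = 0.8s² + 0.16μ², averaged over arms:

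- s = 11: 10.10 (m = 0), 10.35 (m = 3), 11.06 (m = 8).
- s = 20: 18.03, 18.18, 18.59.

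This is a fall of 6 to 10% for m of 0 to 3, and no fall for s = 11 with m = 8.

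**SD of the raw week 8 score.** Variance = 0.8 × (week 8 SD)² + 0.2 × (baseline SD)² + 0.16μ². With equal baseline and week 8 SDs it rises slightly: 20 becomes 20.1 to 20.6, and 11 becomes 11.2 to 12.1. With a baseline SD of 14 and a week 8 SD of 20 it falls to 19.1 to 19.6.

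**Main-trial size (90% power, two-sided 5%, m of 0 to 3).** Keeping 8 as the target and taking only the carried-forward change SD gives 34–36 per arm instead of 40 (SD 11), or 107–109 instead of 132 (SD 20). Taking the carried-forward difference as well gives 53–55 and 167–170. The two uses err in opposite directions.

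**The case against.** **The word may mean something else.** Eligibility requires "Diagnosis of unilateral or bilateral subjective continuous (24 h) tinnitus", so constant may mean always present. That reading is fair for the percept, but the imputed outcomes are severity scores (THI, TFI, VAS, sleep, anxiety and depression). Continuous presence does not make those scores stable over weeks.

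**The contradiction is softer than it looks.** The Introduction speaks of variation between individuals and says untreated participants may improve a little; it does not say that they do. This stands, and is why m is shown as a range that includes zero. The dilution under equal dropout does not depend on m.

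**Unequal dropout is conjecture.** The only dropout figure is 20%, not split by arm. This stands too. Patients are unblinded and only one arm takes medicine, which makes imbalance possible but does not establish it.

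**The shift is small beside the noise.** With 12 per arm the standard error of the difference is SD × √(2/12), or 4.5 to 8.2 points for SD 11 to 20. A shift of 1.6 points is 0.20 to 0.36 of that. The outcomes are secondary, the study is declared unpowered, and caution is promised. This limits the weight but does not supply a reason for the method.

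**The alternative has its own assumption.** A likelihood-based model relies on missing at random, which open-label dropout could breach. True, but that is weaker than assuming no change, and it can be stated openly.

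**Conclusion.** The point holds, with modest weight. The stated reason for carrying values forward conflicts with the article's own account of tinnitus severity, and the visit schedule turns the method into an assumption of no change for anyone lost before week 8. At 20% dropout, equal by arm, unrelated to outcome and before week 8, the expected difference is 6.4 instead of 8. Intervals are about 14 to 17% too narrow with 2 of 12 missing per arm and natural improvement of 0 to 3 points, and less so if improvement is large relative to the SD.

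Two stronger readings are not supported. A reader might infer that the method shrinks the SD and so makes the full-scale trial too small. The change-score SD usually falls, but the raw week 8 SD need not; the article does not say which SD it will use, and passing on both estimates enlarges the main trial. A reader might also infer a bias in favour of BHT. The direction depends on which arm loses more patients, which the article does not give.

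The primary feasibility rates need no imputation and are unaffected.

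**What to change.** - Delete the rationale that tinnitus is constant.
- Make a likelihood-based repeated-measures model on the observed data the main analysis of the clinical outcomes, with arm, visit and their interaction. Keep every randomised patient in the assigned arm, in line with the intention-to-treat statement. Entering baseline as one of the repeated outcomes, rather than only as a covariate, retains patients with no post-baseline visit.
- State the missing-at-random assumption.
- Keep last observation carried forward only as a sensitivity analysis.
- Take SDs for planning the full-scale trial from observed data.

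The cost is a change of analysis wording. No new data are needed, and the mixed-model procedure in SPSS, the package already named, can fit the model. The intervals will be slightly wider, which reflects the information actually collected. Patients lost before week 8 will add little to the estimated effect, so the result still rests on the stated assumption for them.

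### Paired tests within each arm at p < 0.05 add nothing valid about BHT and could be misread as preliminary evidence that it works

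*Protocol article*

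**What the plan says.** Three analyses of the clinical outcomes appear in the Statistical Analysis section of the protocol article.

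- The treatment effect: "The treatment effect will be assessed with mean difference between two groups and confidence intervals of 75%, 85%, and 95" per cent.
- A model: "Exploratory inferential analysis will be performed using repeated-measures ANCOVA".
- Tests within each arm: "Mean differences from baseline to end of treatment in each group will be examined by paired" t-test or Wilcoxon signed rank test.

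One threshold covers all of them: "All statistical tests will be two-sided, and" p below 0.05 counts as significant. The section adds that the pilot lacks power for a group comparison, that such comparisons can mislead when samples are small, and that results will be read cautiously with reference to power. It also expects some preliminary evidence of effectiveness.

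Elsewhere, the Introduction says trial participants "may demonstrate a small but statistically significant improvement, despite receiving no intervention", and uses this to prefer a controlled pilot to an observational study. The Discussion says the counseling-alone arm "will help to control some non-specific treatment effects, such as natural history and regression to the mean". The Inclusion Criteria require "scores above 38 on the Chinese (Cantonese) version of the Tinnitus Handicap Inventory", and the same scale is the first of the secondary outcomes.

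**The concern.** A paired test in the BHT arm asks whether that arm changed, not whether BHT changed it. The change combines any BHT effect with natural improvement, regression to the mean and the response to counseling. Selecting patients above a threshold on the THI-CH and then measuring the THI-CH again makes some average fall likely in both arms. Read alone, the paired test treats the BHT arm as the kind of uncontrolled study that the Introduction argues against.

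Comparing the two p-values does not repair this. A significant change in one arm and a non-significant change in the other is not a test of the difference between arms, and it arises often when the arms do not differ.

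What is at stake is the reading of the pilot's clinical results. With so few patients the between-arm comparison will often be inconclusive, and a within-arm p-value may then be the most striking number available when the article's preliminary evidence is written up and a full-scale trial is considered.

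**Working it through.** **Inputs from the article.** Sample Size Estimation: 10 per arm, 20% dropout, total 24, assumed difference 8, SD 11 to 20. Its figures reproduce: 8/20 = 0.40 and 8/11 = 0.73, against the stated 0.4 to 0.7; 2 × 10 × 1.2 = 24, hence n = 12 per arm with equal arms. Statistical Analysis: two-sided 0.05.

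**Inputs assumed.** The article gives neither the shared improvement m nor the SD of change s. I take m = 3 to 6 points and s = 10 to 15.5. The upper s corresponds to an outcome SD of 20 and a baseline-to-week-8 correlation of 0.7: 20 × √(2 × (1 − 0.7)) = 15.5. BHT has no effect.

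**Paired test in one arm.** The chance p of a significant improvement is the upper tail, beyond the critical t, of a non-central t with 11 df and non-centrality m√12/s. The critical t(11) is 2.201. The arms are independent, so the chance that BHT is significant and control is not is p(1 − p).

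| m | s | m√12/s | p | p(1 − p) |
|---|---|---|---|---|
| 0 | any | 0 | 2.5% | 2.4% |
| 3 | 15.5 | 0.67 | 9% | 8% |
| 3 | 12 | 0.87 | 12% | 11% |
| 4 | 15.5 | 0.89 | 13% | 11% |
| 4 | 10 | 1.39 | 24% | 18% |
| 6 | 15.5 | 1.34 | 23% | 18% |
| 6 | 12 | 1.73 | 35% | 23% |
| 6 | 10 | 2.08 | 48% | 25% |

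The nominal rate in this direction is 2.5%.

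**The valid comparison under the same null.** In simulation (n = 12, s = 15.5, shared improvement 0, 4, 8 or 12 points), a two-sample test on change scores rejected about 5% of the time, two-sided, in all four cases. The shared improvement cancels.

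**Regression to the mean alone.** Assume a source population with mean THI 30 to 50, SD 20 and test-retest correlation r = 0.7 to 0.9, entering only above 38. The expected fall is (1 − r) × 20 × λ, where λ = φ(a)/(1 − Φ(a)) and a = (38 − mean)/20. This gives 0.9 points (mean 50, r = 0.9) to 6.4 points (mean 30, r = 0.7). The paired test is then significant for improvement 5% to 28% of the time with no treatment effect of any kind.

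**Power of the between-arm test.** For the assumed difference of 8 with 12 per arm, the non-centrality is 8/(SD × √(2/12)): 0.98 at SD 20 and 1.78 at SD 11. Power is about 16% and 40%.

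**Gain from baseline adjustment.** With an assumed correlation r = 0.6, the variance ratio is 1 − r² = 0.64 against raw follow-up scores, a cut of 36%. Against change scores it is (1 − r²)/(2 − 2r) = 0.64/0.80 = 0.80, a cut of 20%.

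**The case against.** A reader might infer that the plan will credit BHT with natural improvement. The documents do not support that. The treatment effect is assigned to the between-group difference, the objectives are framed against counseling alone, and the inferential work is labelled exploratory. The primary outcomes are feasibility rates with numeric thresholds, and no p-value enters that decision. Nowhere is a within-arm p-value said to show efficacy. All of this stands: the misattribution needs a later misreading.

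The Introduction should not be pushed further than it goes either. It says participants may show a small improvement, not that they will. A shared improvement of 6 points is 75% of the assumed difference of 8 (6/8), which is hard to call small, so the upper figures are one end of a range.

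The caution statement answers less than it seems to. Its stated reasons are small samples and low power, and its explicit warning concerns comparisons between groups. Referring to power does not tell a reader that a within-arm change is biased as a measure of the BHT effect.

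Two stronger readings should also be set aside. Presenting an unadjusted between-group difference would not be an error, since randomization makes it unbiased; adjustment buys precision. And a numeric criticism of "Subgroup analysis on those with or without hearing loss, and those with unilateral or bilateral tinnitus will be made" would need a split between subgroups that the article does not give, while its small-sample caveat already covers the issue.

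Finally, a per-arm 95% confidence interval excludes zero exactly when the paired t-test gives p < 0.05. Removing the p-values alone would therefore leave the same misreading open.

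**Conclusion.** The point holds as a flaw in a secondary, exploratory analysis. The paired tests carry a formal significance threshold, answer a question that the article's own reasoning makes uninformative about BHT, and are neither labelled descriptive nor barred from use as evidence. Under the assumed 3 to 6 points of shared improvement and SD of change of 10 to 15.5, with 12 per arm and no BHT effect, the false signal in the BHT arm runs at about 9% to 48%, and the misleading contrast between arms at about 8% to 25%. Both ranges depend on inputs that the documents do not supply; the direction does not, provided some shared improvement occurs. The sample size, the feasibility outcomes and the named treatment effect are unaffected.

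**What to change.** 1. Delete the paired t-tests and Wilcoxon signed rank tests.
2. Report mean change per arm descriptively, with a sentence saying that within-arm change includes natural history, regression to the mean and counseling response, and does not inform the BHT effect. This sentence is needed even if the p-values go.
3. State that the between-arm difference and its 75%, 85% and 95% confidence intervals at weeks 8 and 12 come from the baseline-adjusted model (ANCOVA or a mixed model), and that statements about effectiveness rest on that estimate alone.

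Baseline scores are already collected, so no visit, measurement or patient is added. The cost is analysis wording and fewer p-values to report. The return is protection against the misreading and, if the correlation is near the assumed 0.6, tighter intervals.
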